## Abstract

Lumbar intervertebral disc degeneration (DD) disease is one of the main risk factors for low back pain and a leading cause of population absenteeism and disability worldwide. Despite a variety of biological studies, lumbar DD is not yet fully understood, partially because there are only few studies that use systematic and integrative approaches. This urges the need for studies that integrate different omics (including genomics and transcriptomics) measured on samples within a single cohort. This protocol describes a disease-oriented Russian disc degeneration study (RuDDS) biobank recruitment and analyses aimed to facilitate further omics studies of lumbar DD integrating genomic, transcriptomic and glycomic data. A total of 1,100 participants aged over 18 with available lumbar MRI scans, medical histories and biological material (whole blood, plasma and intervertebral disc tissue samples from surgically treated patients) will be enrolled during the three-year period from two Russian clinical centers. Whole blood, plasma and disc tissue specimens will be used for genotyping with genome-wide SNP-arrays, glycome profiling and RNA sequencing, respectively. Omics data will be further used for a genome-wide association study of lumbar DD with *in silico* functional annotation, analysis of plasma glycome and lumbar DD disease interactions and transcriptomic data analysis including an investigation of differential expression patterns associated with lumbar DD disease. Statistical tests applied in each of the analyses will meet the standard criteria specific to the attributed study field. In a long term, the results of the study will expand fundamental knowledge about lumbar DD development and contribute to the elaboration of novel personalized approaches for disease prediction and therapy. Additionally to the lumbar disc degeneration study, a RuDDS cohort could be used for other genetic studies, as it will have unique omics data.

**Trial registration number**
NCT04600544.

## Introduction

Intervertebral disc degeneration is a normal aging process, but in some cases it causes lumbar disc degeneration disease (LDDD) [1,2]. Intervertebral disc degeneration (DD) often begins earlier than degenerative changes in the ligaments, cartilages and other tissues of spinal segment [3]. DD is a major contributor to low back pain [4], but can also proceed without back pain [5–8]. However, LDDD is associated with a lower health–related quality of life [9] and is the leading cause of population absenteeism and disability [10,11]. Intervertebral disc degeneration (DD) is an initiating factor in LDDD and is one of the major contributors to subsequent low back pain [4]. The prevalence of lumbar DD in the general population is extremely high: up to 50% in people aged 30–39 years [2,12]. There is not a single adult who has not at least some degree of degeneration in the intervertebral discs [13]. The list of well-known risk factors of LDDD includes female gender, advanced age [14], obesity, smoking [15], absence of or extreme physical activity [16] and genetic risk factors [17]. However, even in the absence of obvious risk factors, there are cases of LDDD among young people [1,14], as well as progressive severe LDDD requiring a number of surgical interventions.

The biology of intervertebral DD is extensively studied from different points of view. Besides various studies of degenerative disc morphology [18–22] and molecular biology [16,23–25], there is an increasing number of genetic [26,27], transcriptomic [28–30] and proteomic [31–33] studies of intervertebral DD. Thus, based on candidate-gene [34] and genome-wide associated studies (GWAS) [35,36], over 160 genes have now been considered to be potentially involved in intervertebral disc degeneration, although less than ten of them provide strong evidence for the association [34]. More than 500 genes have been highlighted as being expressed differently in degenerative disc tissue and healthy intervertebral discs [37,38]. Moreover, proteomic [31–33] and metabolomic [39] changes have also been detected in degenerative intervertebral discs. Despite a large number of LDDD studies, the exact mechanisms underlying this disease are not yet fully understood, partially because there are only few studies that use systematic and integrative approaches [40]. To our knowledge, there are no large-scale studies that integrate different genomics and other omics data within a single cohort. This complicates the extrapolation of previous findings on an integrative picture of LDDD pathology. Therefore, more integrative omics studies are needed to put all pieces of knowledge together, build a complete picture of the biology of lumbar DD and obtain a deeper understanding of the processes underlying this pathology.

Moreover, the low number of genes reliably and reproducibly associated with LDDD [34] does not explain its high heritability (up to 74%) [41]. It highlights that genetic and transcriptomic studies with greater sample sizes and replication samples are needed.

This protocol describes a study that provides broad opportunities for combining newly acquired and existing knowledge in various fields of genomics, transcriptomics and molecular biology due to its scale and the use of an integrative approach. Not only will this be beneficial for researchers as a resource of fundamentally new information on the mechanisms involved in disc degeneration pathology, it will enrich the list of reliable disease markers and drug targets, expanding the diagnostic and treatment approaches, which is crucial for the development of personalized, accurate and effective treatment of LDDD.

### Research aim and objectives

The main aim of this study is to establish a disease-oriented biobank to facilitate research into the biology of lumbar disc degeneration. Different biological samples (whole blood, plasma, disc tissue) along with MRI imaging, clinical, socio-demographic and various omics data (e.g. genomic and transcriptomic) will be available for researchers and clinicians for a variety of further multi-omics studies. It will lay the groundwork for the development of early diagnostics of LDDD and its personalized treatment.

## Methods and analysis

### Study design and settings

This disease-oriented biobank to study lumbar disc degeneration will be recruited from two centers: the Priorov National Medical Research Center of Traumatology and Orthopedics (Priorov CITO), Moscow, Russia, and the Novosibirsk Research Institute of Traumatology and Orthopedics (NRITO), Novosibirsk, Russia. The study will be performed according to the Helsinki Declaration; the study protocol was approved by the Local Ethical Committee of the Novosibirsk Research Institute of Traumatology and Orthopedics (№034/20 dated 02 Oct 2020) and by the Local Ethical Committee of the Priorov National Medical Research Center of Traumatology and Orthopedics (№1/21 dated 25 Feb 2021). It will be conducted for a period of three years starting from 2021. Patients aged over 18 years with available MRI of the lumbar spine, who signed informed consent and met eligibility criteria, will be recruited. Clinical data and specimens will be collected in three visits as described in Table 1. At the first step, general information about a patient, his medical history and MRI scans of lumbar spine will be obtained. Patients’ biological material (whole blood and plasma) will be sampled in the centers at baseline. Then, from those patients, who will undergo a spine surgery during the treatment disc tissue samples will be gained. Eventually, postoperative clinical data will be collected from operated patients during the follow-up. Over three years, we expect to collect information and biological material from a total of 1,100 patients. A full schematic of the study is presented in Fig 1.

**Fig 1 pone.0267384.g001:**
[figure not shown]
Patient selection. Sample size at various time-points of the project. Expected total sample size is 1,100. *Novosibirsk Research Institute of Traumatology and Orthopedics (NRITO) / Priorov National Medical Research Center of Traumatology and Orthopedics (Priorov CITO). **Conservative treatment.

**Table 1 pone.0267384.t001:** Scheduled procedures for clinical data and sample collection.

	Visit 1—Baseline	Visit 2—Day of surgery^1^	Visit 3–3 months after surgery^2^
Visit Window (±Days)			Day 90 ±14 days
Informed Consent	X		
Eligibility Criteria^3^	X		
Medical History	X		
Anamnesis Vitae	X		
Demographics	X		
Blood samples	X		
MRI	X		
ODI^4^	X		X
VAS^5^	X		X
Indications for surgery		X	
Surgical Procedure		X	
Intervertebral disc samples		X	
Adverse events/Serious adverse events	X	X	X

^1^only for patients subjected to surgery

^2^optional

^3^see Table 2 for details

^4^Oswestry Disability Index (ODI) scale

^5^Visual analogue scale (VAS) for back and leg pain.

All biological samples from NRITO will then be transported to the Institute of Cytology and Genetics (ICG), Novosibirsk, Russia, for long-term storage, further processing and omics profiling, including genotyping of blood samples and RNA sequencing of disc tissue. Priorov CITO will store the specimens on at their place.

### Patient selection and expected sample size

All patients of the two clinical centers aged over 18 with available MRI scans of the lumbar spine, who will sign an informed consent (see S1 File) and meet all the eligibility criteria (Table 2), will be included in the study. All participants will be assessed by the orthopedists and neurologists and grouped into three categories based on their diagnosis: patients with spine surgery, patients with conservative treatment of symptomatic LDDD and other patients with MRI scans of the lumbar spine (see Fig 1). If the reason for the hospital visit is symptomatic LDDD, patients will be divided according to the type of treatment (conservative or surgery) and corresponding ICD-10 codes. If the reason for the hospital visit is other than symptomatic LDDD, the patient will be included in the group of other patients with MRI scans of the lumbar spine in the study, regardless of the ICD-10 diagnosis code. Restrictions on participation in the study for patients with bloodborne pathogens are determined by the requirements of laboratory biosafety.

**Table 2 pone.0267384.t002:** Eligibility criteria.

Inclusion criteria	Exclusion criteria
1. Age over 18; 2. Presence of lumbar MRI scans; 3. Signed informed consent for voluntary participation is provided.	1. Any contraindication or inability to undergo baseline procedures; 2. Prior surgeries at any level of the lumbar spine; 3. Other non-degenerative spinal conditions that may have an impact on subject safety, wellbeing or the intent and conduction of the study; 4. History or presence of HIV, hepatitis B, hepatitis C.

We plan to collect whole blood and plasma samples from not less than 1,100 patients (see Fig 1). The SNP array based whole-genome genotyping and total plasma protein N-glycosylation profiles will be measured for at least 384 participants. Total RNA sequencing expression profiles of approximately 40 disc specimens will be measured.

### MRI imaging, clinical and socio-demographic data

We require each patient from this study to have lumbar spine MRI images. MRI scanning will be performed on a 1.5 Tesla (or higher) tomograph and will include L1-S1 lumbar segments. T1 and T2 weighted images, acquired both in the axial and sagittal planes, will be obtained. Images will be used to assess the disc degeneration grade, presence and type of Modic changes and presence and severity of vertebral endplate defects. Disc degeneration grade will be estimated under the Pfirrmann classification from 1 to 5, with 1 corresponding to a normal disc and 5 corresponding to the most severe degeneration [42]. Modic changes will be evaluated for each endplate (from the lower L1 vertebra to the upper S1 vertebra) on sagittal scans using T1WI and T2WI [43]. Vertebral endplate defects will be ranged from 1 to 6 according to the Rajasekaran classification [44]. Then, total endplate scores (TEPS) will be calculated as the sum of the endplate defect scores of both upper and lower endplates in each L1-S1 spinal segment. Additionally, the height of the intervertebral discs and severity of osteophytes will be estimated based on Jarosz classification [45].

Clinical assessment will include demographic data (sex, age), self-reported ethnicity, height, weight, family status, physical activity, smoking, comorbidity, education level and job type.

All participants will complete the following clinical questionnaires: visual analogue scale (VAS) [46] back and VAS leg estimating the intensity of back and leg pain, correspondingly, and the Oswestry disability index (ODI) [47,48] questionnaire.

### Sample collection, transportation and storage

Samples collected in NRITO will be frozen at -40C (whole blood and plasma) or at -80C (disc samples) and then transferred to ICG for long-time storage at -80C. All biosamples from Priorov CITO will be frozen and stored on site at -80C.

Blood and plasma sampling: from each patient, 13 ml of peripheral venous blood will be collected into two BD Vacutainer 4-ml and 9-ml K2 EDTA tubes (or three 4-ml K2 EDTA tubes depending on availability). The tubes will be labeled with a patient’s unique code. During the first 30 min after blood collection, the 4-ml vacutainer with whole blood will be placed into a test tube rack and transported to the freezer to be stored at -40C. The 9-ml blood tube will be used for plasma extraction according to the plasma extraction protocol (see S2 File). Once the plasma has been extracted, the tubes with plasma will be labeled and placed into the freezer at -40C.

Eventually, all the tubes from NRITO will be transported to ICG in thermoboxes with cooling agents and then placed into freezers at -80C. Samples from Priorov CITO will be stored locally at -80C at once.

Collected plasma samples could be used for cell-free DNA, glycomics, proteomics and metabolomics analyses.

### Disc sampling

During the surgical procedure, the resected fragments of intervertebral discs will be placed into sterile falcon 50-ml tubes and stored in the operating room until the end of the intervention (for no longer than 40 min). The falcons will be labeled with unique codes and transported to the laboratory within 5 min where the discs’ fragments will be put into liquid nitrogen.

Disc samples from NRITO will be transferred to ICG within thermoses with liquid nitrogen and then will be stored in freezers at -80C. Biospecimens obtained in Priorov CITO will be stored on site at -80C.

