### Total RNA profiling

The intraoperative material will be homogenized using TissueLyzer II homogenator (QUAGEN) and total RNA will be extracted and converted to cDNA using a kit for the isolation of total RNA and microRNA from cells and tissues (Biolabmix, Russia) and the M-MuLV–RH First Strand cDNA Synthesis Kit (Biolabmix, Russia), respectively. The amount of extracted RNA and its quality will be estimated using Bioanalyzer 2100 (Agilent).

Total RNA sequencing will be performed using Illumina-HiSeq 4000 under the PE-protocol. A read length of up to 100 bp and a sequencing coverage of 20M are expected. Specimens will be randomly selected for sequencing utilizing the block randomization approach in order to maintain a uniform distribution of optimization characteristics set for genotyping batches. In total, not less than 40 samples will be profiled.

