#### Transcriptomic data analysis

The patient group with available intraoperative disc material (see Fig 1) could be divided into “cases” or “degenerated disc” (grades 4–5 of disc degeneration according to the Pfirrmann classification) and “controls” or “healthy disc” (grades 1–3 of disc degeneration according to the Pfirrmann classification) [44,60].

This division does not influence the scheme of patient recruiting or sample collection but plays a role in the transcriptomic data analysis. The groups will include following ICD-10 codes: M51.1 “Thoracic, thoracolumbar and lumbosacral intervertebral disc disorders with radiculopathy” (cases); M51.3, M51.8 “Other thoracic, thoracolumbar and lumbosacral intervertebral disc degeneration” (controls).

Transcriptomic data obtained in this study will be used for detection of genes differentially expressed in discs between cases and controls. In short, the gene expression data will be mapped [61] onto the reference genome and the quality of the reads will be recalibrated (“Picard Toolkit.” 2019. Broad Institute, GitHub Repository. http://broadinstitute.github.io/picard/; Broad Institute). Subsequently, aiming to reveal the transcriptomic differences in intervertebral discs tissue between cases and controls, we will count the reads and identify differentially expressed genes (DEGs) using the edgeR package [62]. To assess the statistical significance of the results, we will apply a Benjamini-Hochberg correction for multiple testing [63]. DEGs will be filtered by the q-value < 0.05 and divided into up- and down-regulated genes. Finally, the revealed DEGs will be functionally annotated with Gene Ontology terms.

The data will also be used to identify expression quantitative trait loci (eQTLs). We will perform an eQTL analysis of gene expression levels in intervertebral discs using the methodology described in [64]. Resulting regional association summary statistics will be used for gene prioritization.

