One more substantial strength of our study is the assessment of the disc degeneration grade by MRI scans, because this is the most accurate and precise method of DD diagnostics. In LDDD studies based on plain radiography [72] or CT [73], phenotype definition is rather subjective as these approaches provide only indirect evidence of disc degeneration such as disc height loss and osteophytes. Similarly, the use of self-reported questionnaires for LDDD identification [74] is not reliable enough. By contrast, the Pfirrmann grading system of disc degeneration used in the present study is based on MRI scans and estimates the main characteristics of DD by assessing the signal intensity and the height of the intervertebral disc: the more dehydrated the disc is, the more severe degenerative changes are in it [42].

This study has some limitations. First, the expected sample size is modest in comparison with national country-level biobanks or large prospective cohorts. The sample size of the present study is one-fourth as large as the one reported for meta-analysis of LDDD studies by Williams et al. [35]. This limitation is explained by funding, establishing the recruitment period of three years. Nonetheless, the expected number of disc tissue samples (~510) and their transcriptome profiles (~40) is comparable with other omics studies using disc specimens (proteome [33]: 7 cases / 7 controls; metabolome [39]: 60 cases / 21 controls; transcriptome [28]: 39 annulus fibrosus (AF) and 21 nucleus pulposus (NP) samples; [29]: 24 AF and 24 NP samples).

The next limitation of our study is an imbalance between patients with “healthy disc” and “degenerated disc” in the group of patients subjected to surgery. Obviously, patients with “healthy discs” are subjected to spinal surgery under specific circumstances. However, according to our protocol, we can still expect some controls in this group (in total, the expected number of controls is 20). In the groups not subjected to surgery, we expect a ratio between cases and controls to be closer to that in the general population.

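### Freezing of disc tissue is timed from the end of surgery, not from resection, so the wait can vary up to about 45 min and may confound the case-control expression comparison

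*Protocol article*

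**What the plan says.** The Disc sampling section sets the handling rule. The tissue enters its container while surgery is still going on: "During the surgical procedure, the resected fragments of intervertebral discs will be placed into sterile falcon 50-ml tubes". It is then "stored in the operating room until the end of the intervention (for no longer than 40 min", and after that it is "transported to the laboratory within 5 min where the discs’ fragments will be put into liquid nitrogen".

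The Transcriptomic data analysis section uses this tissue to compare cases (Pfirrmann grades 4-5) with controls (grades 1-3), all of them surgical patients. It attaches diagnosis codes to the groups: "M51.1 “Thoracic, thoracolumbar and lumbosacral intervertebral disc disorders with radiculopathy” (cases") and "M51.3, M51.8 “Other thoracic, thoracolumbar and lumbosacral intervertebral disc degeneration” (controls"). The Discussion says of patients with healthy discs only that they "are subjected to spinal surgery under specific circumstances". It expects 20 controls in all.

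Two statements bear on control of handling effects. Total RNA profiling says: "The amount of extracted RNA and its quality will be estimated using Bioanalyzer 2100 (Agilent"). The same section selects specimens for sequencing by block randomization on the characteristics set for genotyping. The Genotyping section lists those as LDDD status, sex, age, availability of disc tissue, birthplace, BMI, physical activity, smoking and blood-sampling date.

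**The concern.** The clock for freezing is tied to an event that has nothing to do with the specimen. A fragment removed near the end of an operation leaves the operating room almost at once; one removed with much surgery still to come waits. The article handles whole blood differently: under Sample collection, transportation and storage, its 30-min limit runs from collection.

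Variation in waiting time that is unrelated to group only adds noise. It becomes bias if cases and controls differ in mean wait and if some measured expression levels change with the wait. Such genes could then enter the list of differentially expressed genes without any link to degeneration. Benjamini-Hochberg correction limits chance findings but does not remove a systematic shift between groups. A check of RNA amount and quality does not measure the time since resection. If the interval is not captured when the specimen is taken, it cannot be recovered later. That matters beyond the first 40 or so profiles, because about 510 disc samples are expected and samples are to be kept for fifteen years.

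**Working it through.** The article derives no sample size, power or error rate from the 40-min limit, so there is no stated figure to reproduce. The check has four steps.

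**1. Permitted range.** Inputs from Disc sampling: at most 40 min in the operating room and at most 5 min of transport.
- Longest: 40 + 5 = 45 min, taking the 40 min to start when the fragment enters the tube.
- Shortest: a few minutes. The 5 min is an upper limit on transport, so no exact minimum follows, and a ratio of longest to shortest would mean little.

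**2. Can the wait differ by group?** Set side by side, the sections give different diagnosis codes for cases and controls, and special circumstances for surgery on healthy discs. Neither states operation type, duration or timing of resection by group. A difference is plausible but not documented.

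**3. How much would a difference matter?** This is an illustration only. From the article: 20 controls and about 40 profiles, so 40 - 20 = 20 cases if every control is sequenced. My assumptions: within-group SD of waiting time 10 min; a time-sensitive gene shifts by b = 0.25 or 0.5 residual SD per 10 min; no true case-control effect; a two-sided normal test at 0.05 per gene, without multiplicity adjustment. With D the difference in mean wait in minutes:
- shift = b × D/10
- SD = √(1 + b²), because the wait itself varies by 10 min within groups
- SE = SD × √(2/20)
- false-positive rate = 1 - Φ(1.96 - shift/SE) + Φ(-1.96 - shift/SE)

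Example, D = 10 and b = 0.25: shift = 0.25; SD = √1.0625 = 1.031; SE = 1.031 × 0.316 = 0.326; shift/SE = 0.767; rate = 12.0%.

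| Difference in mean wait | b = 0.25 | b = 0.5 |
|---|---|---|
| 0 min | 5.0% | 5.0% |
| 5 min | 6.7% | 10.9% |
| 10 min | 12.0% | 29.3% |
| 20 min | 33.5% | 80.7% |

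These are rates for one time-sensitive gene at an unadjusted 0.05. They are not the expected share of false findings after the q < 0.05 filter, which would also depend on how many genes are time-sensitive.

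**4. Can it be adjusted for afterwards?** Yes, if it is recorded, but at a price that rises with the imbalance. With equal groups and a within-group SD of 10, the squared correlation of wait with group is r² = (D²/4)/(D²/4 + 100), and adjustment inflates the variance of the group effect, at a given residual variance, by 1/(1 - r²).
- D = 10: r² = 25/125 = 0.20; inflation 1/0.80 = 1.25.
- D = 20: r² = 100/200 = 0.50; inflation 1/0.50 = 2.

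Shortening the wait at source is therefore better than relying on the model alone.

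**The case against.** The strongest reply is that the harm is conditional. Diagnosis codes are not procedures, and without a group difference in mean wait there is no case-control bias: the first row of the table stays at 5.0%. The wait is bounded, RNA quality is checked, and the article gives no rate at which disc expression changes over 45 min. The main aim is the biobank, and the expression comparison is one planned use of it. All of this stands, and it limits the point to a possible confounder of unknown size.

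A reader might go further in three ways that the article does not support.
- **That operations differ between cases and controls.** No section says so; they may.
- **That the two limits contradict each other.** The parenthesis reads naturally as a cap, whichever comes first. What is left is an unhandled case: if more than 40 min of surgery remains after resection, the text does not say what happens to the tube. Total length of operation is not the trigger, since a long operation with late resection raises no difficulty.
- **That waiting times go unrecorded, or that tissue is held without cooling or stabiliser.** The article is silent on these, and a condensed article may leave them to a laboratory procedure. Table 1 schedules the surgical procedure and the disc samples at Visit 2, so the type of operation may be available as a proxy, though it does not give the interval.

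It is also fair to say that balancing the RNA selection on waiting time may help little among controls. With 20 expected and about 40 profiles planned, most or all of them may have to be sequenced. The gain there would come from choosing among cases and from the model.

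**Conclusion.** The point holds in a limited form. The stated rule lets time from resection to liquid nitrogen vary from a few minutes to about 45 min, according to how much surgery remains. Nothing in the listed selection characteristics accounts for it. It is a plausible confounder of a comparison of roughly 20 v 20, but bias requires both a group difference in mean wait and genes that respond to it, and the article quantifies neither. The illustrative rates (12.0%-29.3% at 10 min, 33.5%-80.7% at 20 min) rest on assumed values and show only that an imbalance well inside the permitted range could matter. This is a cheap improvement to a stated handling rule, worth making before collection because the interval cannot be reconstructed afterwards. It is not an error that invalidates the plan.

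**What to change.** 1. In Disc sampling, start the clock at resection: send the labelled tube to the laboratory once the fragment has been removed, without waiting for surgery to end. State the existing 40 min as a maximum from resection, and say what is done with a specimen that exceeds it. Freezing inside the operating room is not needed.
2. Record the time of resection and the time of freezing for every disc specimen.
3. In Total RNA profiling, add the resection-to-freezing interval to the selection characteristics, to be used where there is a choice of specimens.
4. In Transcriptomic data analysis, include the interval as a covariate in the edgeR model or in a sensitivity analysis, and report its distribution in cases and controls.

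The cost is an earlier walk to the laboratory (Disc sampling allows 5 min for it), repeated over about 510 expected specimens at two centres, plus two time fields per specimen. The model loses one degree of freedom: with 40 profiles and only intercept and group fitted, residual degrees of freedom go from 40 - 2 = 38 to 40 - 3 = 37. If the groups turn out to be imbalanced, there is also the variance inflation shown in step 4 of the working. The operation itself does not change.
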